#### *Analysis of PCA composite axes and survey sum scores*

The analysis for these outcomes will involve two steps. In step 1, we will estimate the tetrachoric correlations between the 12 variables from the TEC survey which will subsequently be analyzed using a principal components analysis (PCA). We will use standard methods to objectively determine the # of axes to retain and interpret including: levelling out of scree plot, eigenvalue threshold of  $> 1$ , parallel analysis, and factor loadings. If the number of axes to interpret is ambiguous, then the research team will use study specific knowledge to evaluate the results from the PCA to make decisions on which axes to include in further analysis. In step 2, we will analyze the composite scores

from the PCA analysis using the same GLMM approach as previously described with the exception that the distributional assumption will be normal with an identity link function. The estimate of interest will be the mean difference in PCA scores between the intervention and control. In addition to the PCA composite scores, we will also analyze the sum scores (i.e., the sum of the responses over all of the questions). The analytic approach will be the same for that as for the composite axes. If we find that our conclusions are similar between the two approaches (PCA and sum scores) then we will focus our interpretation on the sum scores as these provide more straightforward interpretation compared to the PCA composite scores, even though in theory PCA scores are more valid.

## **Subgroup analyses**

The primary subgroup analyses of interest will be to assess whether there is evidence of heterogeneity in treatment effects among clusters by stratifying the analyses by healthcare facility (“horizontal” analysis) and heterogeneity in treatment effects across time by stratifying analyses across periods (“vertical” analysis) (analysis terminology as per White et al., 2018).

In addition to the stratified analyses of primary interest (across clusters and periods), we will also assess the difference between the intervention and control groups for the following subgroups:

- Care Status (in care, LTFU)
- Intervention and control group (TEC vs Exit comparison only)
- Sex
- Age (<25, 25-44, >45)
- Clinic Size and Type
- Improvement index by facility
- PCC dose - when finalized
- Advanced HIV Disease at enrollment in care (WHO Stage 3 or 4, CD4<200)

For those subgroups that appear to have a difference with regard to the intervention effect, we will formally test for an interaction between the intervention and the subgroup.

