**Figure S1. Panel A- Stepped wedge cluster randomized design, Panel B- Distribution and Timing of Enrolments and Measurements.** Panel A. The intervention was assigned in random sequence to four groups of clinics during each of four temporal periods. Empty white boxes represent the control status while the green represent the intervention status during that Period and Group. Periods were planned to be six months each, but Period 2 (started in February 2020) coincided with regional health emergency related to COVID-19 and was extended due to health systems challenges. Panel B. Gray boxes indicate Groups and Periods that were not included for particular analyses. Client experience was assessed cross-sectionally in Groups 2, 3, and 4 across all periods. Missed visits were assessed for all visits for all Groups during all periods using Electronic Health Record (EHR) data. Retention in Care using EHR data was assessed in Group 1 & 4 among individuals who made a visit during Period 1 with outcome ascertainment occurring in Period 3 (i.e., 15 months later). Treatment success was assessed in Group 1 & 4 with baseline measurements collected in Period 1 and outcome ascertainment in Period 3. 15 months after intervention experience.

[figure not shown]

**Figure S2. PCC Multicomponent Strategy.** We see the multicomponent intervention as operating through three pathways involving capability, opportunity and motivation. The immediate outcome was changes in health care worker behaviour, which then was thought to influence the client experience, client retention and clinical outcomes.

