#### TEC survey population

|                   | Period 1                                                          | Period 2                                                               | Period 3                                                              | Period 4                                                               | Totals per wave |
|-------------------|-------------------------------------------------------------------|------------------------------------------------------------------------|-----------------------------------------------------------------------|------------------------------------------------------------------------|-----------------|
| Wave 1            |                                                                   |                                                                        |                                                                       |                                                                        |                 |
| Wave 2            | Control
30 patients x 4
facilities =
120 patients | Intervention
30 patients x 4
facilities =
120 patients | Intervention
15 patients x 4
facilities =
60 patients | Intervention
15 patients x 4
facilities =
60 patients  | 360 patients    |
| Wave 3            | Control
15 patients x 4
facilities =
60 patients  | Control
15 patients x 4
facilities =
60 patients       | Intervention
15 patients x 4
facilities =
60 patients | Intervention
15 patients x 4
facilities =
60 patients  | 240 patients    |
| Wave 4            | Control
15 patients x 8
facilities =
120 patients | Control
15 patients x 8
facilities =
120 patients      | Control
30 patients x 8
facilities =
240 patients     | Intervention
15 patients x 8
facilities =
120 patients | 600 patients    |
| Totals per period | 300 patients                                                      | 300 patients                                                           | 360 patients                                                          | 240 patients                                                           | 1200 patients   |

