#### Study Population:

TEC patients are drawn from patients who were adults over 18 years of age at time of recruitment, on or had been on treatment, with at least one clinical visit between 17th August 2019 and 17th November 2021 (which we used to define the study population) in study facilities. TEC patients were included both patients in care (who were recruited in the waiting room through systematic sampling of every kth patient where k depended on the facility size) as well as patients who had been in care but were lost to follow up (at least 30 days late for a visit) who were approached through the phone or contact through tracing in the field. The patients were drawn from facilities in waves 2, 3 and 4 during both control and intervention periods (Figure)

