## **Quantile regression**

In addition to variability in the central tendency as measured by the mean, there is also likely to be strong variability at the extremes of the data that may better captured via a quantile-regression analytic approach. This approach permits fitting regression lines through various quantiles of the data (e.g., 90th percentile, 10th percentile) to test how individuals at distributional extremes respond to the intervention. We will stratify these analyses by facility and examine how the response of different outcomes vary over time and in response to the intervention. To these ends, models will fit a regression line over the course of the study with an indicator variable for the intervention. We will also test whether the slope varies by the intervention by fitting a treatment x intervention interaction.

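### The facility-stratified TEC analyses have no concurrent control, so a time change shared by all facilities can look like differences between facilities; the period-stratified analyses have a control contrast only in Periods 2 and 3

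*Combined protocol and SAP*

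**What the plan says.** SAP section 4.0, Subgroup analyses, gives two stratified analyses priority. The first is horizontal, to assess "heterogeneity in treatment effects among clusters by stratifying the analyses by healthcare facility", that is, by a separate fit in each facility. The second is vertical: "heterogeneity in treatment effects across time by stratifying analyses across periods". A formal interaction test follows only for subgroups that appear to differ. The section does not say how calendar time is handled inside a facility stratum, or which periods contain both conditions.

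The Quantile regression section also works facility by facility: "We will stratify these analyses by facility and examine how the response of different outcomes vary over time". It fits a regression line over the course of the study with an intervention indicator, and tests for a changing slope by "fitting a treatment x intervention interaction".

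Wave 1 contributes no TEC data: "The patients were drawn from facilities in waves 2, 3 and 4 during both control and intervention periods". The legend to Figure S1 agrees: "Client experience was assessed cross-sectionally in Groups 2, 3, and 4 across all periods". The same legend places the COVID-19 emergency in Period 2.

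The main TEC model (SAP 4.0, Analysis) is different. It pools facilities, with a random facility effect and categorical period, and allows linear or spline time if that fits better.

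**The concern.** The main model separates the intervention from calendar time by comparing facilities that are in different conditions in the same period. A fit inside one facility gives up that comparison. Intervention always comes after control there, so the estimate is a before-after difference, and any secular change goes into it unless the assumed trend happens to be right.

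The crossover date differs by wave, so one shared secular change enters the facility estimates in different amounts. An analysis that looks for variation among facilities could then find variation that reflects only the rollout schedule. The facility samples are also small enough for sampling error alone to produce a wide spread. On the vertical side, nothing in the SAP tells the reader that two of the four strata contain no control contrast.

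**Working it through.** **Inputs.** The TEC survey population table in SAP 4.0 gives these planned surveys per facility:

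| Wave | Facilities | P1 | P2 | P3 | P4 | Control / intervention |
|---|---|---|---|---|---|---|
| 2 | 4 | 30 C | 30 I | 15 I | 15 I | 30 / 60 |
| 3 | 4 | 15 C | 15 C | 15 I | 15 I | 30 / 30 |
| 4 | 8 | 15 C | 15 C | 30 C | 15 I | 60 / 15 |

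The TEC sample size section of the SAP gives a 65% positive baseline, ICC 0.2, 80% power and p < 0.05 (taken as two-sided).

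**The plan's own figure.** The SAP states a detectable difference of 15.0 points for the pooled comparison. I used the Hussey-Hughes generalised least squares variance with categorical period, total variance 0.65 × 0.35 = 0.2275, between-facility part 0.2 × 0.2275 = 0.0455 and within-facility part 0.182. The multiplier is 1.960 + 0.842 = 2.802.
- A flat 15 surveys per facility-period: SE 0.0524, detectable difference 14.7 points, power at 15 points 81.7%. This matches the SAP.
- The unequal cells in the table: SE 0.0455, detectable difference 12.8 points, power 90.9%.

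The pooled figure is not in dispute. The SAP gives no precision for the stratified analyses.

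**Horizontal: identification.** In one facility, four period indicators plus the intervention indicator make 5 columns of rank 4 in every wave, so the effect is aliased with period. An intercept, a linear trend and the intervention have rank 3 of 3, so the effect can be estimated once a line is assumed. With early and late exposure coded separately by period plus a line, waves 2 and 3 have rank 4 of 4, but wave 4 has 3 of 4 because it has no late period.

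**Horizontal: bias from a shared step s starting in Period 2.** Unadjusted bias is the share of intervention surveys after the step minus the share of control surveys after it.
- Wave 2: 60/60 - 0/30 = 1.0, so 1.0s.
- Wave 3: 30/30 - 15/30 = 0.5, so 0.5s.
- Wave 4: 15/15 - 45/60 = 0.25, so 0.25s.

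With a linear trend, weighted by cell size, the biases are 1.0s, -0.5s and -0.545s. In wave 2 the step coincides with the intervention indicator, so no trend term removes any of it. As an illustration, take an assumed 10-point step and the same true effect everywhere. Facility effects would then spread by 10 - 2.5 = 7.5 points unadjusted, and by 10 + 5.45 ≈ 15.5 points with the line.

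**Horizontal: sampling error on one binary item, ignoring time.** SE = √[p(1-p)(1/n0 + 1/n1)], with the same p in both conditions. The 35% negative rate is the complement of the SAP's 65%. The 20% is an assumption.

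| Wave | SE, p = 0.20 | 95% limits | SE, p = 0.35 | 95% limits |
|---|---|---|---|---|
| 2 | 0.089 | ±18 | 0.107 | ±21 |
| 3 | 0.103 | ±20 | 0.123 | ±24 |
| 4 | 0.115 | ±23 | 0.138 | ±27 |

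Power for 65% against 80% in one facility is 35%, 25% and 17% in waves 2, 3 and 4. A linear term raises the SEs at 35% to 0.168, 0.275 and 0.189.

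**Vertical.** Control/intervention facilities are 16/0, 12/4, 8/8 and 0/16 in Periods 1 to 4. Periods 1 and 4 hold 300 + 240 = 540 of 1,200 surveys (45%). For the other two periods at ICC 0.2, the variance of a facility mean is 0.0455 + 0.182/n, which is 0.0516 at n = 30 and 0.0576 at n = 15.
- Period 2: √(0.0516/4 + 0.0576/12) = 0.133; × 2.802 = 37 points.
- Period 3: √(0.0576/8 + 0.0516/8) = 0.117; × 2.802 = 33 points.

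At ICC 0.05 the figures are 23 and 21 points. The difference between the Period 3 and Period 2 effects, fitted jointly, has a detectable size of about 23 points at either ICC.

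**Is the question answerable when pooled?** A joint model with 16 facility intercepts, 3 period contrasts and 16 facility-specific intervention effects has 35 columns and rank 35, so the facility effects are identified once period is shared.

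**The case against.** Several points on the other side stand.
- A straight line is not the only way to handle time. The SAP names splines and, in its sensitivity analyses, visit date. A quadratic is also estimable: the third difference of the indicator is 1, -2 and 1 in waves 2, 3 and 4. That fit uses up all four period means, however, and the step (third difference 1) then gives 1.0s, -0.5s and 1.0s. The effect still rests on the assumed shape.
- A reader might infer that every facility's effect is fully confounded with COVID-19. The documents do not support that. Wave 3 has control data in Period 2, and wave 4 has control data in Periods 2 and 3. Confounding with the COVID era is complete only for the 4 wave 2 facilities.
- The stated aim is heterogeneity among clusters. A time effect shared by all facilities cancels between facilities of the same wave. The SAP does not restrict the comparison in that way.
- A vertical stratum without a contrast gives no estimate, which is not a misleading one. Protocol 8.1.2 combines period-specific estimates, so empty periods would drop out. Period 4 still allows early against late exposure.
- The interaction in the quantile section is a wording slip. The sentence concerns a slope over time, so time by intervention was evidently meant. That model also includes a time trend, so it is not a bare before-after fit. Table S6 reports pooled columns, and the appendix contents list no facility-specific TEC effects.
- The ±18 to ±27 limits apply to single binary items, not to the sum or PCA scores.

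The objection does not remove the main defect. Followed as written, the facility strata discard the concurrent controls, and the resulting bias differs by wave.

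**Conclusion.** The point holds for the subgroup and quantile analyses of a secondary outcome, and a change should be made. Facility-specific effects are not identified without an assumption about time. A shared step from Period 2 enters them in proportions 1.0, 0.5 and 0.25 by wave, or 1.0, -0.5 and about -0.55 with a line. Comparisons across waves, and absolute facility effects, are therefore unsafe; comparisons within a wave are protected from a shared time effect. Vertical control contrasts exist in Periods 2 and 3 only, with detectable differences of about 37 and 33 points at ICC 0.2.

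The size rests on the planned cell counts, a step beginning exactly at Period 2, and assumed negative-answer rates of 20% to 35%. The step size s is unknown.

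A reader might go further and infer that the heterogeneity analyses are worthless, or that the TEC result itself is confounded with the pandemic. Neither follows. Within-wave comparisons and two randomised period contrasts remain, and the pooled estimate with categorical period is unaffected.

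**What to change.** 1. Replace the facility-stratified fits with the pooled TEC mixed model. Keep categorical period and add a random facility-by-intervention effect. Report its variance with an interval, and the shrunken facility effects. State that the variance will be imprecise: there are 16 facilities, 8 of them with only 15 planned intervention surveys each.
2. State that vertical intervention-control estimates come from Periods 2 and 3 only, give their low precision, and describe Period 4 as early against late exposure.
3. Fit the quantile regression pooled across facilities, with categorical period and facility-clustered inference such as a facility bootstrap. Correct the interaction to time by intervention.

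The cost is SAP wording and a modified model. No further data collection is needed, and the main TEC analysis stays as it is.

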| Behavioural Target                                                                  | 
 
Knowledge and skills to deliver person-centred care
 
Increased salience, motivation, and identification of opportunities to deliver more person-centred care
 
Increased of PCC behaviors, including being more welcoming, empathy, improved communication, shared decision making, and leveraging discretionary power to better accommodate client needs.
 
 |
| Temporality                                                                         | 
 
Training HCW on PCC at 0m for Group 1, 7m for Group 2, 13m for group 3 and 19m for Group 4
 
Mentorship begins immediately after first batch of HCWs trained in PCC
 
Synthesis meeting 6 weeks after training
 
Client experience data review meetings every 3 months
 
Incentive for best performing facility every 6 months
 
                |
| Dose                                                                                | 
 
PCC training done once for two days for each HCW
 
Weekly mentorship visits to facility till study end
 
                                                                                                                                                                                                                                                             |

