**Training and Facilitation:** The PCC intervention started with a two-day interactive training program that focused on strategies to improve the quality of interactions, included modules on PCC principles, client-provider communication, and stress management. Trainings were held outside the facility and targeted all HCWs (i.e., lay health workers, counsellors, medical officers, clinical officers, nurses, pharmacists, data managers) as well as facility support staff (e.g., security guards, cleaners), recognizing that interactions with any facility staff could influence the client experience and that HCWs commonly transfer between departments. After training was complete, study clinical mentors (i.e., 14 nurses and clinical officers trained in practice facilitation for person-centered care that oversaw 2-3 facilities each) provided ongoing support at facilities through approximately twice weekly mentorship facility visits throughout the intervention. Mentorship visits involved short lectures, role plays, and facilitated group discussion sessions that were tailored based on mentor assessment of facility needs and were delivered in a supportive manner that recognized the challenges faced by HCWs. During COVID-19 periods, trainings occurred in smaller groups (e.g., 5-10 HCWs rather than 40 HCW at a time).

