**Figure S4. Intervention Fidelity**

Frequency of visits that mentors made to health facilities weekly. Mentors visited facilities at least once a week throughout the study (facilities intervention phase). However, we see that there were more visits in Group 1 & 2 and this is on account of increased support that PCC study mentors rendered to facilities in response to COVID-19 between May 2020 and August 2020.

| Table S2. Top five most reported mentoring activities as a proportion of all reported activities.   |                                  |          |          |          |
|------------------------------------------------------------------------------------------------------------|----------------------------------|----------|----------|----------|
| Top 5 commonly reported mentoring activities                                                               | Period 1                         | Period 2 | Period 3 | Period 4 |
|                                                                                                            | % of total activities per period |          |          |          |
| Relationship building                                                                                      | 29%                              | 31%      | 33%      | 31%      |
| One-on-one HCW observation and mentoring                                                                   | 25%                              | 17%      | 28%      | 24%      |
| Supporting facility context improvements (facility-prioritized system-level changes driven by data review) | 10%                              | 12%      | 5%       | 8%       |
| Meeting with facility leaders (Overall In-Charge, ART In-Charge or Departmental Heads)                     | 0%                               | 10%      | 6%       | 7%       |
| Service to support facility (side-by-side work)                                                            | 2%                               | 3%       | 2%       | 3%       |

Footnote: Mentors recorded their activities during mentorship visits to the health facilities in Mentor Activity Logs. These are the 'Top five most reported mentoring activities' (out of 17 main activities). Mentors spent most of their time in 'relationship building' and 'one-on-one mentoring' and this points to the importance of interpersonal interaction.

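### Two planned TEC subgroups, PCC dose and facility improvement index, are not baseline factors, so their intervention-versus-control contrasts lack the protection of randomisation and can mislead

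*Combined protocol and SAP*

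**What the plan says.** In SAP 4.0, Subgroup analyses, stratification by facility and by period comes first. A second list of eight items follows, introduced by "we will also assess the difference between the intervention and control groups for the following subgroups". Sex, age and care status stand there beside "Improvement index by facility" and "PCC dose - when finalized". Where a subgroup seems to differ, "we will formally test for an interaction between the intervention and the subgroup". No unit, data source, time window or cut-off is given for the dose or the index, and nothing marks them as non-randomised.

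Other places bear on this:

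- The SAP is version 3.1 of 15 February 2022. Its TEC study population is defined by visits up to 17 November 2021.
- The TEC model (SAP 4.0, Analysis) has a facility random effect, categorical period, and exposure coded as control, early (up to 6 months) or late (over 6 months).
- Protocol 8.2, Table 1, shows the measurement platform running in every wave and period. Training, coaching and incentives start only at a wave's step.
- Figure S4 reports of mentor visits that "there were more visits in Group 1 & 2 and this is on account of increased support that PCC study mentors rendered" in response to COVID-19.
- The appendix's Intervention Description says mentorship sessions were "tailored based on mentor assessment of facility needs". It states visit frequency in two ways: "Weekly mentorship visits to facility till study end" in the strategy table, and "approximately twice weekly mentorship facility visits throughout the intervention" in the text on training and facilitation.

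**The concern.** A subgroup contrast in a randomised trial is safe when the subgroup is fixed before treatment starts. Dose is not: it comes into being at crossover and depends on what was then delivered. The index is undefined, but its name denotes change over time, so it very probably uses data from after the step. Sorting facilities on such variables can group them by chance variation, by local trend or by wave, and then present the sorting as effect modification. A later interaction test does not repair this, because it tests the same non-randomised contrast.

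At stake is interpretation. A dose gradient would be read as showing how much mentoring is needed, and an index gradient as showing that some facilities respond and others do not. Leaving the dose definition open after TEC visits had ended adds freedom to choose cut-offs with the data in hand.

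**Working it through.** The plan gives no figure for these subgroups, so there is none to reproduce. The check has a structural part and a simulation part.

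**Structure of a dose subgroup**

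1. *Patient- or period-level dose.* If dose means training, coaching and incentives, it is zero in every control period (Protocol Table 1). No stratum with positive dose holds a control observation, so the planned contrast does not exist there.
2. *Facility-level dose.* Every TEC facility has a control period, so a contrast exists. TEC excludes Wave 1. If dose is counted in visits, Figure S4 implies that high-dose TEC facilities may lean to Wave 2.
3. *A Wave-2-only stratum.* Wave 2 is control in Period 1 and intervention in Periods 2 to 4. With period indicators P1 to P4, intervention = P2 + P3 + P4 = 1 − P1. That is an exact combination of the intercept and the period terms, so the effect is not identified. The early and late indicators sum to the same column. A linear or spline time trend, which the SAP allows if model fit favours it, would identify the effect only through the assumed shape of the trend.

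**Simulation under no intervention effect**

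Inputs from SAP 4.0: 16 facilities (4, 4 and 8 in Waves 2, 3 and 4). Surveys per facility in Periods 1 to 4 are 30/30/15/15, 15/15/15/15 and 15/15/30/15, which gives 1,200. Positive experience is 65% and the ICC is 0.2. Assumed, because the documents give no values: the SD of facility drift (a facility's own shift between control and intervention time, unrelated to the intervention), the correlation of dose with drift or baseline, and 90 responses per condition for a separate survey. Facilities are split at the median of the index or dose, and their intervention-minus-control changes are compared by a two-sample t-test across facilities, 4,000 runs per row. This stands in for the SAP's interaction test and is not identical to it.

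| Sorting variable | Assumed drift SD (points) | High-half minus low-half gap (points) | p<0.05 |
|---|---|---|---|
| Index from the same TEC responses | 0 | 16.9 (+8.0 vs −8.9) | 100% |
| Index from a separate survey | 0 | 0.0 | 5.0% |
| Index from a separate survey | 5 | 4.0 | 9.1% |
| Index from a separate survey | 10 | 11.4 | 34% |
| Dose unrelated to drift | 5 | 0.1 | 4.5% |
| Dose correlated 0.3 to 0.5 with drift | 5 | 2.1 to 3.6 | 5.8% to 8.7% |
| Dose correlated 0.5 with drift | 10 | 7.1 | 15% |
| Dose correlated −0.5 with drift | 10 | −6.9 | 14% |
| Dose tied 0.5 to 0.9 to low observed baseline | 0 | 1.9 to 3.5 | 5.6% to 8.5% |

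**Hand check of the first row.** Within-facility variance is 0.65 × 0.35 × (1 − 0.2) = 0.182. The variance of a facility's change is 0.182 × (1/n control + 1/n intervention):

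- Wave 2: 0.182 × (1/30 + 1/60) = 0.0091, SD 0.095
- Wave 3: 0.182 × (1/30 + 1/30) = 0.0121, SD 0.110
- Wave 4: 0.182 × (1/60 + 1/15) = 0.0152, SD 0.123

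The average SD over 16 facilities is (4 × 0.095 + 4 × 0.110 + 8 × 0.123)/16 = 0.113. Splitting a centred normal variable at its median gives half-means of ±0.798 × SD, or about ±9 points. Sampling noise alone produces the pattern.

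**Second model.** A null simulation with facility and period fixed effects (800 trials; assumed facility SD 10 points and trend +3 points per period) gave +9.1 and −8.6 for a split on observed change, with an overall estimate of −0.1. Adding an assumed facility-by-period SD of 10 points gave +13.0 and −13.0, overall −0.5.

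**The case against.** The strongest case against has four parts.

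- *The pattern is not inevitable.* A reader might infer that both subgroups must show a gradient even if the intervention does nothing. The documents do not support that. It is automatic only if the index is built from TEC responses, and the SAP does not say so. The appendix says the facility dashboard used SMS and Exit surveys, which points elsewhere. Dose unrelated to facility trend and baseline gave no false gradient. This part stands, and the claim is limited to what can happen.
- *The dose mechanism can be over-read.* A reader might infer that visit frequency was set by facility need, or that high dose simply is Wave 2. The tailoring sentence describes what sessions contained, not how often mentors came. The lean to Wave 2 applies only if dose is counted in visits. Dose could instead be the share of staff trained, and Table S1 gives no split by wave. This also stands.
- *If high dose were Wave 2, the stratum would follow a randomised sequence.* True, but it would then have no concurrent control, and the fault becomes loss of identification.
- *The consequence is small.* These are two of eight additional subgroups for a secondary outcome. Table S4 shows only care status, sex and age, and the appendix contents list no dose or index effect table. A reader might infer that reported TEC results are distorted; nothing here shows that.

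Exploratory dose analysis of a complex intervention is legitimate when it is defined and labelled. The SAP does neither and gives these items the same contrast and test as baseline factors.

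**Conclusion.** The point holds in limited form. Dose is a post-rollout variable and the index very probably is one, so both are outside the protection of randomisation. Either can show a false dose-response or responder pattern under no effect.

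- *Index:* in the conditional worst case, a gap of about 17 points, against a planned detectable difference of 15.0 points for the overall contrast. With a separate survey the gap runs from 0 to about 11 points over assumed drift SDs of 0 to 10.
- *Dose:* from about −7 to +7 points over the assumptions tried, and zero if dose is unrelated to trend and baseline.

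The identification failures for patient- or period-level dose and for a Wave-2-only stratum follow from the design and need no simulated quantity. The effect is confined to secondary subgroup analyses of a secondary outcome; the main TEC estimate is not touched.

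**What to change.** Remove both items from the intervention-versus-control subgroup list and from the interaction tests in SAP 4.0. Report delivered dose (staff trained, mentor visits per facility-week from the Mentor Activity Logs) descriptively by wave and period. Rest exposure-response claims on the prespecified early/late contrast, whose timing follows the randomised step. Clinic size and type, already listed, can serve for facility-level effect modification.

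If either analysis is kept, define its source, window and cut-offs before analysis, do not build the index from TEC responses, and label the result non-randomised and exploratory.

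Separately, reconcile the weekly and twice-weekly mentorship statements in the Intervention Description. Figure S4's report of at least one visit a week is compatible with both and does not settle it.

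The cost is SAP wording and the loss of two exploratory displays.
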